## **B. BACKGROUND AND RATIONALE**

Early landmark clinical trials have demonstrated the benefits of early administration of antiplatelet medications (primarily aspirin) to enhance saphenous vein graft patency, at a minimum for the first year post-CABG (1,2). These studies established that the 1-year expected saphenous vein graft occlusion rate is approximately 10-15% (1-3). More recent data has shown that long-term adherence to statin medications, with anti-lipid and anti-inflammatory properties, also significantly improves early, mid-term and late graft patency (19,20). Intraoperative quality assurance tools, such as completion angiography and/or transit time Doppler flowmetry have also been shown to have benefits to reducing technical errors which may improve early graft patency (21-23), although their benefit on clinical outcomes has not been consistently supported in clinical trials (6,24,25).

### **I. Choice of conduits – arterial versus saphenous vein**

The choice of conduit for CABG has been shown to impact graft patency. The excellent early and late patency of *in situ* left internal thoracic arteries (LITA) (26,27) has stimulated the use of other arterial grafts, such as the right ITA and the radial artery (RA) (7,28-30). The ongoing Arterial Revascularization Trial, recruiting 3,000 patients, is the key RCT aiming to confirm the observational findings that bilateral ITA grafts purport improved clinical outcomes compared to a single ITA (31). Randomized trials, including one by our study investigators, have shown that the radial artery is as good or superior to a saphenous vein graft with respect to early and mid-term patency for CABG surgery (7,32,33). Total arterial revascularization with bilateral ITA and a RA is a well described contemporary CABG revascularization strategy aimed to accrue the aforementioned benefits. The Copenhagen Arterial Revascularization Randomization Patency and Outcomes Trial enrolled 331 patients to either bilateral ITA and a RA versus LITA and SVGs. Results at 1-year post-CABG showed equivalent clinical outcomes, with a tendency towards more early sternal healing complications in the total arterial cohort (34,35). However, at 14 months Muneretto et al show similar mortality, yet significantly lower rates of non-fatal MI, graft occlusion and recurrence of angina, in an elderly cohort of patients undergoing total arterial revascularization using a LITA and radial versus LITA plus SVGs (36,37).

Although still debated, the overall evidence from the literature suggests that that while two arterial grafts provide improved clinical outcomes compared to a sole LITA, a third arterial graft may not provide any significant benefit (34,35,38,39). Target coronary vessels/lesions are also limited for ITA and RA, and concerns regarding arterial graft spasm, string sign, graft site ischemia remain and poor wound healing including sternal infection (for bilateral ITAs) are notable (7,40-43). Furthermore, recently population-based studies indicate that multiple arterial grafting is used for only a quarter of patients undergoing isolated CABG (44). As such, ***SVGs remain an important conduit for patients undergoing CABG using a LITA or a LITA plus a second arterial graft.***

## **II. “No touch” technique of SVG harvesting**

There are no systematic reviews concerning “no touch” SVG harvesting. A single Swedish cardiac surgical centre has published studies demonstrating that harvesting the SVG with a cushion of surrounding fat and without vein graft distension, the so-called “no touch” technique, significantly improved patency compared with conventional methods, i.e. stripping the vein of all adventitial tissue and distension with a balanced salt solution prior to implantation (45-47) (18 month patency: “no touch” 95% vs. conventional 89%,  $p=0.10$ ; 8.5 year patency: “no touch” 90% vs. conventional 76%,  $p=0.01$ ). By multivariate analysis, the “no touch” technique was strongly protective (OR 3.7, 95% CI 1.4-9.6,  $p=0.007$ ). There is significant biological data from graft specimens that the “no touch” technique preserves vein architecture and nitric oxide synthase (47,48). The major limitation regarding the putative benefit of the “no touch” technique of vein harvesting is that the data has all been derived from a single centre. Replication of these results in multiple centres is required prior to the technique being widely adopted. However, the concept of avoiding trauma from SVG handling was also explored by a group in Bristol, UK, led by Angelini (49). They used a biodegradable external sheath to cover porcine SVG prior to use in a carotid bypass porcine model. While they found significant reductions in medial and intimal thickening in the SVGs, when applied in a phase I human trial (the Extent Study), results were not favourable. Conversely, post-hoc analysis from the PREVENT IV trial, and recent observational data published in NEJM, show that endoscopic harvesting of SVG results in significantly worse graft patency and clinical outcomes, likely due to increased trauma during harvesting and subsequent endothelial injury and dysfunction (5, 50). Overall there is clear equipoise to performing a multi-centre randomized clinical trial to validate the excellent single-centre results shown by Souza et al and determine whether the “no touch” technique is reproducible, feasible and generalizable (45-48).

## **III. The use of fish oil supplementation**

Interest in fish oil supplementation originated following the initial discovery that dietary fish was associated with decreased cardiovascular risk in Greenland Eskimos (51). Several mechanisms have been postulated to explain the potential benefits of fish oils, including lipid lowering (52-55), plaque stabilization (56), anti-thrombotic (57), anti-inflammatory (58) or anti-arrhythmic properties (59-61). The American Heart Association recommends a daily intake of 1 gram daily, either in the form of fish or fish oil supplements as secondary prevention for patients with coronary artery disease (52). A meta-analysis, published earlier this year in BMJ, reviewed results from 12 studies totaling 32,779 patients (54). There was no significant improvement with fish oil supplementation for the endpoints of sudden death (OR 0.81, 95% CI 0.52 - 1.25) or all-cause mortality (OR 0.92, 95% CI 0.82 - 1.03) while cardiac deaths were reduced significantly (OR 0.80, 95% CI 0.69 - 0.92). The overview was heavily weighted by 2 studies, GISSI-Prevenzione (62,63) and JELIS primary and secondary prevention trials (64). The earlier post-MI DART trial in 2,033 men (not included in the meta-analysis) showed a 29% risk reduction in all-cause mortality in those with increased intake of fish-oils, with or without supplementation (65). Additional recent trials not included in the meta-analysis, GISSI-HF (66) and OMEGA (67) involving approximately 11,000 additional patients, revealed conflicting results. In the GISSI-HF trial, all-cause mortality was reduced 9% (adjusted HR 0.91, 95% CI 0.83 - 0.99) while benefits were not observed in OMEGA (ACC 2009, unpublished). Trials have consistently showed that for secondary prevention, the dose of at least 1g of fish-oil per day is required to accrue the most benefits (in an approximately 1.2:1 ratio of the active ingredients DHA:EPA) (55). Two studies have been completed in CABG patients. In a 160 patient RCT, fish oil supplementation started 5 days preoperatively was associated with a decreased incidence of postoperative atrial fibrillation (68). The role of fish oils on 1-year postoperative SVG patency was assessed in a 610 patient RCT by Eritsend et al (69). Fish oils were

protective for SVG patency (OR 0.77, 95% CI 0.60 - 0.99) and serum n-3 phospholipid levels were inversely correlated with graft occlusion. In addition to these potential gains, fish-oils are low-cost, usually well tolerated, and have been used in larger clinical trials in association with other evidence-based therapies (62,63,64,66,67).

#### **IV. Risks to the safety of participants**

There are no known additional risks associated with the study as compared to the usual standard of care (besides the inherent risks associated with CABG). Bypass surgery carries some risks, including a chance of heart damage (less than 5%) and death (less than 2%), stroke (about 5%). Although there are risks, the potential life-saving benefits of CABG surgery outweigh the risks. Additional complications associated with CABG surgery may include: bleeding, renal failure, infection, difficulty breathing, and/or arrhythmias (particularly atrial fibrillation). Both SVG harvesting techniques are used routinely in the centres participating in this study. The “no touch” technique may result longer harvesting times; however, there are no known risk associated with this. Damage to the saphenous nerve is inevitable when harvesting the SV by this technique; however, this also occurs frequently when using the conventional technique.

The most common side effect of taking fish oil supplements is a fishy aftertaste. This occurs in a moderate number of people. Gastrointestinal disturbance (which can include diarrhea, halitosis, eructation and nausea) is a low risk associated with taking fish oils. Taking fish oils with food rather than on an empty stomach has been shown to lower the risk of fishy aftertaste and GI disturbances. Some interactions may also occur between fish oil supplements and aspirin, other NSAIDs and herbs such as garlic and ginkgo. Such interactions might be manifested by increased susceptibility to bruising, nosebleeds, hemoptysis, hematemesis, or hematuria. Most who take fish oil supplements and the above drugs or herbs do not suffer from these problems. When they do occur, they are rare.

## **2 STUDY OBJECTIVES**

The objective of the pilot phase of the study is to determine the number of eligible patients of the total isolated CABG patients, the consent rate, adherence to the protocol including rate of follow-up cardiac CT angiography, medication discontinuation and the overall incidence of the primary outcome. Achieving a recruitment rate of 1-2 patients/centre/month will determine if the study will proceed to the full phase III trial.

The primary objective of this study for the **Surgical Arm** is to determine whether a novel atraumatic (“no touch”) technique of pedicled saphenous vein graft (SVG) harvesting results in a lower **proportion of study SVGs** that are totally (100%) occluded on 1-year post-CABG angiography and death due to cardiovascular or unknown causes, compared to conventional SVG harvesting techniques, in patients undergoing CABG.

The primary objective of this study for the **Pharmacological Arm** is to determine whether N-3 polyunsaturated fatty acid (fish oil) oral supplementation results in a lower **proportion of patients** with  $\geq 1$  graft (study SVG, non-study SVG or arterial graft) totally (100%) occluded at 1-year post-CABG angiography and death due to cardiovascular or unknown causes, compared to those who received placebo.

The secondary objectives for the **Surgical Arm** are to determine whether:

- i. The “no touch” technique of SVG harvesting results in a lower ***proportion of study SVGs*** that have a significant stenosis (50-99%) on 1-year post-CABG angiography compared to conventional SVG harvesting techniques.
- ii. The incidence and severity of adverse SVG harvesting events at 1-year post-CABG (infection, haematoma, swelling, neuropathy, quality of life measures) are similar between the “no touch” and conventional groups of patients.
- iii. The incidence of the composite of non-fatal myocardial infarction (MI) (using new definition, see Section 5.5), all-cause mortality, and repeat revascularization (redo CABG or percutaneous coronary intervention [PCI]) perioperatively and at 1 year is lower in the “no touch” versus conventional group of patients.

The secondary objectives for the **Pharmacological Arm** are to determine whether:

- iii. Fish oil supplementation results in a lower ***proportion of patients*** with  $\geq 1$  graft with a significant (50-99%) stenosis at 1-year post-CABG angiography, compared to those who received placebo.
- iv. The incidence of the composite of non-fatal MI (using new definition, see Section 5.5), all-cause mortality, and repeat revascularization (redo CABG or PCI) perioperatively and at 1 year is lower in the fish oil versus placebo group of patients.

The tertiary objectives for the **Surgical Arm** are to determine whether the incidence of the composite of non-fatal myocardial infarction (MI) (using old definition, see Section 5.5), all-cause mortality, and repeat revascularization (redo CABG or PCI) perioperatively and at 1 year is lower in the “no touch” versus conventional group of patients.

The tertiary objectives for the **Pharmacological Arm** are to determine whether the incidence of the composite of non-fatal MI (using new definition, see Section 5.5), all-cause mortality, and repeat revascularization (redo CABG or PCI) perioperatively and at 1 year is lower in the fish oil versus placebo group of patients.

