## **Secondary Outcomes**

***Surgical Intervention:*** The two groups will be compared with respect to:

- i. The number of study SVGs with a significant (50-99%) stenosis on 1-year CTA.
- ii. The number of study SVGs with a significant stenosis or total occlusion at 1-year CTA.
- iii. The incidence of and severity of adverse SV harvesting events by 1-year (infection, haematoma, swelling, neuropathy).
- iv. The incidence of the composite endpoint of perioperative and 1-year non-fatal MI (using new definition, see “Early perioperative myocardial infarction (within 72 hours of surgery)” below), all-cause mortality, repeat revascularization (redo CABG or PCI) (major adverse cardiac events, MACE) and stroke.

***Pharmacological Intervention:*** The two groups will be compared with respect to:

- i. The proportion of patients with  $\geq 1$  graft with a significant (50-99%) stenosis on 1-year CTA.
- ii. The proportion of patients with  $\geq 1$  graft with a significant stenosis or total occlusion at 1-year CTA.
- iii. The proportion of venous and arterial grafts considered separately with total occlusion and/or stenosis, defined above.
- iv. The incidence of the composite endpoint of perioperative and 1-year non-fatal MI (using new definition (see “Early perioperative myocardial infarction (within 72 hours of surgery)” below), death, repeat revascularization (redo CABG or PCI) (major adverse cardiac events, MACE) and stroke.

NB: Graft occlusion determines the primary endpoint and graft stenosis, the secondary endpoint, as graft occlusion is generally of greater clinical importance than stenosis. Graft occlusion is the primary mode of SVG failure 1 year postoperatively (7).

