### **8.3 Statistical Methods**

The primary comparison for the 2 main study questions (“no touch” vs. conventional SVG harvesting [primary endpoint: study SVG occlusion]; fish oil supplementation vs. placebo [primary endpoint: proportion of patients with >1 graft occluded]) will be performed using a Chi-square test according to the intention-to-treat principle. A test for interaction will be tested similarly and with logistic regression. Statistical significance is assumed for  $p < 0.05$ . The secondary graft occlusion endpoints, graft stenosis, or graft occlusion or significant stenosis, will also be tested with Chi-square or Fisher’s tests where appropriate, considering graft stenosis as a dichotomous variable, as well as logistic regression treating graft stenosis as an ordinal variable. Additional modeling will be performed post hoc with logistic regression, generalized estimating equation and bootstrapping techniques, to evaluate covariates of graft occlusion (7,18,71). Variables of interest in addition to the usual demographic factors include: open vs. endoscopic vein harvesting, serum lipid values; study centre; surgeon; time period of patient entry (to address a possible learning effect); timing of postoperative angiography; parameters related to the distal coronary artery target such as, size, quality, and factors related to the specific coronary artery grafted including the severity of the proximal stenosis. Other categorical outcomes (major cardiac events and vein harvest site complications) will also be compared with either Chi-square or Fisher’s Exact test where appropriate. The harvest site infection scores will be tested using t tests.

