## 8.5 Sample size calculation

### A. SURGICAL ARM

The sample size estimation is based on the current prevalence of 1-year SVG occlusion using the conventional harvesting technique to be 20% (5,6). We consider a 30% relative risk reduction (RRR) in graft occlusion using the “no touch” technique to be a clinically important difference, consistent with RRRs reported for previous interventions to improve graft patency (antiplatelet therapy, use of statins post CABG, radial versus saphenous veins) and very conservative in terms of Souza’s clinical trial results (45,46). A sample size of 615 patients in each group will provide 80% power for a 2-tailed alpha of 0.05, to identify a RRR of 30% (20% occlusion rate in the control/ conventional harvesting group, to 14% in the experimental/”no touch” group – see Table 2a).

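### Surgical secondary objective ii asks whether harvest-site events are similar, but Section 8.3 gives only tests of difference, which cannot establish similarity

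*Protocol*

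**What the plan says.** Section 2 (Study Objectives), surgical arm, secondary objective ii, is to determine whether the incidence and severity of adverse harvesting events at 1 year, including "neuropathy, quality of life measures) are similar between the “no touch” and conventional groups of patients". The Evaluation Criteria row of the synopsis uses the same wording. The neighbouring surgical objectives i and iii look for a lower rate with no-touch, so the choice of *similar* for objective ii appears deliberate.

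Section 5.5 (Secondary Outcomes) words the matching outcome neutrally. The two groups are compared with respect to "The incidence of and severity of adverse SV harvesting events by 1-year". Quality of life appears in the Section 2 list but not in this one.

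Section 8.3 (Statistical Methods) names the analysis: "Other categorical outcomes (major cardiac events and vein harvest site complications) will also be compared with either Chi-square" or Fisher's exact test, and "The harvest site infection scores will be tested using t tests". The decision rule is "Statistical significance is assumed for" p<0.05. The protocol gives no equivalence or non-inferiority margin, no confidence-interval criterion and no power statement for harvest-site events. The surgical sample size in Section 8.5 concerns graft occlusion only.

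**The concern.** A Chi-square, Fisher or t test takes equality as its null hypothesis. It can reject equality, but failing to reject does not show that two techniques are alike within any stated tolerance. To conclude similarity, one must rule out an excess larger than some bound, and the protocol sets no bound. The stated objective and the named analysis therefore do not fit together.

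An excess of leg complications with no-touch is plausible on the protocol's own account. Section 5.1 describes no-touch as a longitudinal lower-leg incision with surrounding tissue taken. It allows endoscopic harvest in the control group, and gives fewer local wound complications as one reason institutions use it. If a non-significant comparison were reported against an objective worded this way, it could be taken as evidence that the techniques are equally safe for the leg when the data still allow a material excess.

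**Working it through.** **1. The plan's own figure.** Section 8.5 states "A sample size of 615 patients in each group will provide 80% power for a 2-tailed alpha of 0.05", for "20% occlusion rate in the control/ conventional harvesting group, to 14% in the experimental". With pooled variance, two-sided, no continuity correction:

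n = [1.96·√(2·0.17·0.83) + 0.8416·√(0.20·0.80 + 0.14·0.86)]² / 0.06² = 614.1, rounded up to 615. Dividing by 0.80 for missing angiography gives 768.75, rounded up to 769 per group.

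The stated figures reproduce. They do not address harvest-site events.

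**2. Inputs for the illustration.**
- Group size: 1,550 / 2 = 775 per surgical group (Sections 8.2 and 8.5, equal allocation). This assumes that harvest-site outcomes are known for every randomised patient.
- Test: two-sided 0.05, pooled two-proportion test (Section 8.3).
- Control complication rate: not in the protocol. Assumed 3% to 10% for infection; 20% is added to represent a commoner outcome.
- True excess: assumed 1.5-fold.

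**3. Chance of p>0.05 when a 1.5-fold excess is real.** With p̄ the mean of the two rates,

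power = Φ( [d·√775 − 1.96·√(2p̄(1−p̄))] / √(p₁(1−p₁) + p₂(1−p₂)) )

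| Control vs no-touch | Φ argument | Power | Chance of p>0.05 |
|---|---|---|---|
| 3% vs 4.5% | −0.406 | 34.2% | 66% |
| 5% vs 7.5% | 0.073 | 52.9% | 47% |
| 10% vs 15% | 1.019 | 84.6% | 15% |
| 20% vs 30% | 2.604 | 99.5% | under 1% |

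The pattern depends on how the excess is expressed. For a fixed 3-point excess, the chance of p>0.05 is 33% at a 5% control rate, 54% at 10% and 70% at 20%. For a fixed 5-point excess at a 20% control rate it is about 35%.

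**4. A single non-significant result.** Take 78/775 (10.1%) with conventional harvest and 102/775 (13.2%) with no-touch.
- Difference 3.1 points; p̄ = 180/1,550 = 0.116.
- z = 0.0310 / √(2·0.116·0.884/775) = 1.90, p = 0.057.
- Unpooled standard error 0.0163; 95% CI 0.0310 ± 1.96·0.0163, that is −0.1 to +6.3 points.

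This result is not significant, yet it is compatible with an excess of more than 6 points.

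**5. What an interval could support at this size.** The 95% CI half-width, 1.96·√(2p(1−p)/775), is 1.7, 2.2 and 3.0 points at rates of 3%, 5% and 10%. That is narrower than the margin the trial could reliably exclude. With equal true rates, one-sided 0.025 and 80% power, the smallest such margin is (1.96 + 0.8416)·√(2p(1−p)/775):
- 5% control rate: 2.80·0.01107 = 3.1 points
- 10%: 2.80·0.01524 = 4.3 points
- 20%: 2.80·0.02032 = 5.7 points

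**The case against.** No sentence in the protocol says that p>0.05 means similar. Section 8.3 says only that these outcomes will be compared, and Section 5.5 is neutral. On this view one word in the synopsis and Section 2 is out of line with the rest. A margin for a secondary safety outcome, and the reporting of confidence intervals, are often left to an analysis plan, and a Chi-square test does not prevent either. Harvest harm is also watched in other ways: Section 8.4 has the data safety monitoring board follow vein harvest site infections and weigh benefit against risk, and the visit schedule has leg wound assessments at 30 days, 3 months and 1 year. Finally, the larger miss rates belong to assumed, rare infection rates. Section 1 calls saphenous nerve damage inevitable with no-touch and frequent with conventional harvest, so neuropathy may be much commoner, and a 1.5-fold excess in a common outcome would rarely be missed.

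Most of this stands and limits the point. A reader might infer that the protocol commits to declaring the techniques similar when p>0.05, that such a result would support adoption of no-touch, or that this is the trial's main harm question. The documents say none of these; the objective is one secondary objective of one arm. What the objection does not remove is the mismatch. The protocol itself sets a similarity objective and itself names the tests, and an analysis plan that followed Section 8.3 would inherit the problem. Monitoring and wound checks help to detect harm but do not supply a criterion for similarity.

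**Conclusion.** Wrong as written, with modest weight. The analysis named in Section 8.3 cannot support the conclusion that surgical secondary objective ii asks for. This holds for the Chi-square and Fisher tests of complications and equally for the t tests of infection scores, and it does not depend on any assumed rate.

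The practical size does depend on assumptions, since the protocol gives no harvest-complication rates. The 66%, 47% and 15% figures illustrate infection at assumed control rates of 3%, 5% and 10%, a 1.5-fold excess and 775 patients per group. They should not be carried over to commoner outcomes such as neuropathy.

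**What to change.** 1. Reword objective ii in the synopsis and Section 2 to agree with Section 5.5: to compare the techniques, or to estimate the difference between them, on harvest-site events. Settle at the same time whether quality of life belongs in this outcome, because the two lists differ.
2. In Section 8.3, add that each harvest-site outcome will be reported as no-touch minus conventional with a 95% confidence interval (a risk difference for complications, a mean difference for infection scores) alongside the named tests, and that p>0.05 will not be read as similarity.
3. Only if the sponsor wishes to keep a similarity claim: base it on the upper confidence limit lying below a margin that is clinically justified and fixed before unblinding. The margins in step 5 of the working show what 775 per group could support. They are not proposals for what is acceptable.

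Items 1 and 2 take a few sentences and add no patients, visits or data. Item 3 costs more, because the outcomes have different base rates and one margin may not serve them all. The downside in either case is that a similarity claim becomes harder to make.
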